#### Hypotheses

The hypothesis for health economic analyses is that the total cost of health care will be lower in the intervention group compared to the control group. Regarding quality of care, the hypothesis for patient reported outcomes is that perceived quality of care as well as overall satisfaction with received care in the NH is significantly better in the intervention croup compared to the control group, even after adjusting for relevant confounding variables. The hypotheses for nursing staff/physicians reported outcomes are that a) the perceived quality of medical/nursing care is significantly better in the intervention group compared to the control group; and b) the perceived quality of medical/nursing care is evaluated significantly better after conducting the intervention compared to baseline.

#### Data analysis

Data will be collected from claims data, audits, telephone interviews, focus groups, and questionnaires (residents, nursing staff and physicians).

Claims data will be used to conduct economic analyses. It will be evaluated to what extent the claiming of benefits (indicators 1–5) differs between both groups regarding time and certain characteristics of the residents (age, gender, care level/care degree, dementia). Subsequently, cost indicators will be aggregated on a residential level. The resulting sum will equate the overall cost of the medical benefits claimed, including project costs. With a cost-benefit analysis, it will be examined to what extent the total cost differs between intervention and control group. Remaining differences between the two groups will be addressed using propensity score adjustment [27]. Results may also be used for budget-impact-analyses from a health insurance company’s perspective. Lastly, quality of life will be linked to the total cost of medical care with a cost-effectiveness analysis. Thereby, improvements in quality indicators such as ‘perceived quality of care’, ‘overall satisfaction with care’, ‘perceived state of health’ and ‘quality of life’ will be analyzed in relation to the costs of medical resource utilization by calculating incremental cost effectiveness ratios.

Because health care costs are not normally distributed, a generalized linear model (GLM) with a gamma distribution and log link transformation will be used for data analysis [28]. To account for the multi-level-structure of the data, a random intercept will be added on the regional or NH level. Finally, regression estimates will be converted back to costs for interpretation. Incremental cost effectiveness ratios and corresponding confidence intervals will be estimated using seemingly unrelated regressions [29].

For the peer assessment, the basis of valuation for the audits will be based on data in the CCC. For non-patient related organizational aspects of the intervention, data will be collected in telephone interviews. Both analyses will be integrated in the report.

Focus group interviews will be recorded. The content-analytical evaluation of the audio recordings will be based on an approach by Mayring [30] using the ATLAS.ti software [31]. The sample size was chosen based on experiences with previous multicenter studies.

Data collection by questionnaires will apply to residents as well as nursing staff and physicians. Due to numerous factors, the intervention will probably improve residents’ quality of life to a lesser extent than quality of care. For this reason, no clear statistically significant superiority is postulated. However, quality of life will be included in the cost-effectiveness analysis to control for unexpected effects of the intervention. In accordance with previous intervention studies, a non-responder rate of 60% is assumed [32, 33]. The statistical analysis strategy is the same used with cost data (GLM; taking into consideration the multi-level-structure as well as propensity score adjustment). It is essential to account for the multi-level-structure, since differences between facilities are to be expected. For nursing staff and physician questionnaires, a non-responder rate of 30% is assumed. Subgroup analyses will control for potential differences between professional/occupational groups.

Data will be analyzed using IBM SPSS Statistics for windows [34], MPlus [35] and Stata [36]. Throughout the study, alpha levels will be fixed at α = 0.05 for all statistical tests.

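### The ICER and its confidence interval are the planned cost-effectiveness result, but the plan's own hypotheses lead to a negative ratio whose size and sign cannot be read

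*Protocol article*

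**What the plan says.** Under Data analysis, the article ends the economic analysis with a cost-effectiveness step. Four resident-reported indicators (perceived quality of care, overall satisfaction, perceived state of health, quality of life) "will be analyzed in relation to the costs of medical resource utilization by calculating incremental cost effectiveness ratios". The measure of uncertainty is also fixed: "Incremental cost effectiveness ratios and corresponding confidence intervals will be estimated using seemingly unrelated regressions".

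The expected direction of each component is stated elsewhere in the article:

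- **Cost.** Under Hypotheses, "the total cost of health care will be lower in the intervention group compared to the control group". The total is net of the intervention's own cost: "The resulting sum will equate the overall cost of the medical benefits claimed, including project costs".
- **Perceived care and satisfaction.** Also under Hypotheses, "perceived quality of care as well as overall satisfaction with received care in the NH is significantly better in the intervention croup".
- **Quality of life.** Under Data analysis, "the intervention will probably improve residents’ quality of life to a lesser extent than quality of care", and then "For this reason, no clear statistically significant superiority is postulated". It stays in the economic analysis all the same: "quality of life will be included in the cost-effectiveness analysis to control for unexpected effects of the intervention".

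The article names no net-benefit measure, cost-effectiveness plane, acceptability curve, or rule for dominance or for an effect near zero.

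**The concern.** An ICER is the cost difference divided by the effect difference. It works as a price per unit of effect when the two differences have the same sign and the effect is well away from zero. The plan's hypotheses point away from that situation in two ways, each concerning different denominators.

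For perceived care and satisfaction, the hypothesised outcome is lower cost with better effect. The ratio is then negative. A larger saving, which is good, and a smaller benefit, which is bad, both make it more negative. The dominated outcome (higher cost, worse effect) is negative too, so the figure alone does not show which group won.

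For quality of life, the denominator may be small compared with its standard error. The ratio can then change sign by chance, and an interval on it may be very wide, unbounded or misleading, depending on how it is built.

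At stake is the cost-effectiveness part of the health economic primary outcome: if the trial succeeds as hypothesised, its planned summary is the one that tells the reader least.

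**Working it through.** **The plan's own figure.** The article gives no number for the ICER. The nearest is the sample size: 1 + 0.01 × (50 − 1) = 1.49, and 1.49 × 253 = 376.97, rounded up to 377 per group. This reproduces. The effect size behind 253 is not stated.

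**Ordering and sign of the ratio.** Illustrative values, not from the article: cost difference ΔC in money units, effect difference ΔE in scale units, and value λ = 5000 per scale unit. Net benefit is λ·ΔE − ΔC.

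| ΔC | ΔE | ICER = ΔC/ΔE | Net benefit |
|---|---|---|---|
| −1000 | +0.25 | −4000 | +2250 |
| −2000 | +0.25 | −8000 | +3250 |
| −1000 | +0.10 | −10000 | +1500 |
| +1000 | −0.25 | −4000 | −2250 |
| −1000 | +0.01 | −100000 | +1050 |
| −1000 | −0.01 | +100000 | +950 |

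Row 2 (a larger saving) and row 3 (a smaller benefit) both move the ratio further below row 1, although one is better than row 1 and the other worse. Rows 1 and 4 have the same ratio but opposite conclusions. Rows 5 and 6 are almost the same result, yet the ratio jumps from one extreme to the other. Net benefit behaves sensibly throughout.

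**How often the ratio would be negative.** Cost and effect differences were simulated as independent normals in SD units, with 800 respondents per group and design effect 1.49 (effective 800/1.49 = 537). With an assumed perceived-care effect of 0.25 SD, the ratio is negative in 95% of draws at a cost difference of −0.10 SD and in about 100% at −0.25 SD.

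**Stability of the quality-of-life denominator.** Inputs:

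- 2000 residents in about 40 homes per group, and intra-cluster correlation 0.01 (Sample size).
- 60% non-response (Data analysis), so 0.4 × 2000 = 800 respondents, or 800/40 = 20 per home.

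Design effect = 1 + 0.01 × 19 = 1.19. SE of the standardised difference = √(2 × 1.19/800) = 0.0545.

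Probability that the effect's 95% interval includes zero, for true difference d: Φ(1.96 − d/SE) − Φ(−1.96 − d/SE). The last column uses the stated design effect of 1.49 instead, giving SE = √(2 × 1.49/800) = 0.0610.

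| Assumed d (SD) | SE 0.0545 | SE 0.0610 |
|---|---|---|
| 0 | 95% | 95% |
| 0.05 | 85% | 87% |
| 0.10 | 55% | 63% |
| 0.15 | 21% | 31% |
| 0.20 | 4% | 9% |
| 0.25 | 0.4% | 1.6% |

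When that interval includes zero, a Fieller set for the ratio is not a finite interval. With d = 0.05 SD, a cost difference of −0.25 SD and the design effect of 1.49, the estimated effect is below zero in about 21% of draws, and the central 95% of simulated ratios runs from about −48 to +46 in SD units.

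**The case against.** The components are planned separately. Total cost is named within the health economic primary outcome, the economic hypothesis concerns total cost alone, and the questionnaire outcomes have their own comparison. If cost falls and perceived care improves, that pair shows dominance without any ratio. This stands. A reader might infer that the economic result as a whole could not be interpreted; the article does not support that. The weakness is confined to the ratio and its interval.

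A reader might also infer that the plan expects no quality-of-life difference, so that the ratio's interval must be unbounded. That goes too far on two counts. The article expects some improvement of unstated size and declines only to postulate significant superiority; at 0.20 SD the instability largely disappears. And unboundedness is a property of a Fieller set, while the article names seemingly unrelated regressions without saying how the interval is formed. Another construction could look finite, but a finite look would not remove the instability when the denominator is small.

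It can be said that net benefit, the plane and a dominance rule belong in a full economic analysis plan, and nothing in the article excludes them. This stands in part: their absence is no fault in an article. But the article does choose the ratio and an interval on it, and that choice fits its own hypotheses badly.

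Finally, net benefit needs a money value per unit of effect. The measures are a newly developed care questionnaire, a modified ZUF-A-7 and the WHOQOL-OLD, and the article gives no such value. This is a real limitation of the remedy.

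**Conclusion.** The point holds in a limited form. For perceived care and satisfaction, the hypothesised result gives a negative ratio with no usable ordering, which a dominated result can match exactly. This follows from the stated signs and needs no effect size; only the frequencies of 95% and about 100% rest on assumed effects and on zero correlation between cost and effect.

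For quality of life, the concern depends on the size of the gain, which is not stated. It is serious at 0.05 to 0.10 SD (the effect's interval includes zero in 85% to 55% of trials), moderate at 0.15 SD (21%) and minor at 0.20 SD (4%). These figures assume 800 respondents per group, 20 per home and an intra-cluster correlation of 0.01.

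This is a stated summary measure worth changing before analysis. It does not threaten the total-cost or questionnaire comparisons.

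**What to change.** For each of the four indicators:

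1. Report incremental cost and incremental effect, each with its confidence interval, and the cost-effectiveness plane.
2. Make incremental net benefit, λ·ΔE − ΔC, the main cost-effectiveness result over a prespecified range of λ per scale unit, with the acceptability curve. Start the range at zero, where net benefit is simply the cost saving and matches the cost hypothesis.
3. State dominance where cost and effect favour the same group.
4. Quote an ICER only when the two differences have the same sign and the effect is clearly away from zero. This keeps the ratio available for lower cost with lower effect, where it does have a meaning. Items 1 and 2 are reported in every case.

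**Cost.** No new data collection, and mainly a change of wording, with two conditions. The scales are not QALYs, so the λ range is a judgement and must be shown as a range, not a single threshold. The joint distribution also requires that a resident's costs can be linked to that resident's questionnaire. The Summative evaluation section describes control-group claims as anonymised and all questionnaire data as anonymous, so the sponsor should confirm whether linkage is possible. If it is not, the cost-effect correlation must be an assumption, varied in sensitivity analysis.

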## Discussion

Exploring and developing new interventions to improve living conditions of residents of long-term care NHs is crucial. Aside from detrimental effects on individual quality of life, the cost of long-term care NHs has become an increasing financial burden on society. Since a considerable number of hospitalizations could be avoided, this project will determine if improved coordination of medical care and an optimized collaboration of nursing staff and physicians can reduce the number of hospital admissions and ambulance transportations. To our knowledge, this study is the first to develop a complex intervention to positively and efficiently influence quality and cost of care in NHs as well as evaluate the intervention’s feasibility in a controlled design.

## Abbreviations

CCC: CoCare Cockpit
CoCare: Coordinated medical care
GLM: Generalized linear models
GP: General practitioner
KVBW: Association of Statutory Health Insurance Physicians Baden Wuerttemberg
NH: Nursing home
ZGGF: Centre for Geriatric Medicine and Gerontology
